## Abstract

**Background:**

Nodding syndrome is a poorly understood neurological disorder of unknown aetiology, affecting several thousand children in Africa. There has been a consistent epidemiological association with infection by the filarial parasite, *Onchocerca volvulus* and antibodies to leiomodin and DJ-1, cross-reacting with *O.volvulus* proteins, have been reported. We hypothesized that nodding syndrome is a neuro-inflammatory disorder, induced by antibodies to *O.volvulus* or its symbiont, *Wolbachia,* cross-reacting with human neuron proteins and that doxycycline, which kills *Onchocerca* through effects on *Wolbachia,* may be used as treatment.

**Methods:**

This will be a two-arm, double-blind, placebo-controlled, randomised phase II trial of doxycycline 100 mg daily for six weeks in 230 participants. Participants will be patients’ ages≥8 years with nodding syndrome. They will receive standard of care supportive treatment. All will be hospitalised for 1–2 weeks during which time baseline measurements including clinical assessments, EEG, cognitive and laboratory testing will be performed and antiepileptic drug doses rationalised. Participants will then be randomised to either oral doxycycline (Azudox®, Kampala Pharmaceutical Industries) 100 mg daily or placebo. Treatment will be initiated in hospital and continued at home. Participants will be visited at home at 2, 4 and 6 weeks for adherence monitoring. Study outcomes will be assessed at 6, 12, 18 and 24-month visits. Analysis will be by intention to treat. The primary efficacy outcome measure will be the proportion of patients testing positive and the levels or titires of antibodies to host neuron proteins (HNPs) and/or leiomodin at 24 months. Secondary outcome measures will include effect of the intervention on seizure control, inflammatory markers, cognitive function, disease severity and quality of life.

**Discussion:**

This trial postulates that targeting O.*volvulus* through drugs which kill *Wolbachia* can modify the pathogenic processes in nodding syndrome and improve outcomes. Findings from this study are expected to substantially improve the understanding and treatment of nodding syndrome.

**Trial registration:**

Registered with clinicaltrials.gov ID: NCT02850913 on 1st August, 2016.

## Background

Nodding syndrome is a complex neurolo**g**ical disorder of unknown aetiology. The disease burden is unknown but it is estimated that there are about 10,000 affected children in eastern and central Africa. Of these, about 3000 live in Northern Uganda [1, 2].

The first reports of nodding syndrome came from Tanzania in the 1960’s [3]. Subsequent cases were reported from Liberia [4], South Sudan [5–7] and Uganda [8, 9]. The disease affects previously normally developing children characterized by bouts of repetitive head nodding (the pathognomonic feature). Symptoms develop in children between the ages of three and 18 years, and initially, the head nodding occurs in association with feeding, a cold breeze or cold weather [7, 10, 11]. Over the years however, this is complicated by multiple types of seizures, malnutrition, cognitive and physical decline [1, 7, 10, 12].

There have been many studies of environmental, infectious, toxic and genetic factors to determine aetiology but the cause remains unknown to date [13–15]. On the other hand, a consistent epidemiologic association has been documented between nodding syndrome and infection with *Onchocerca volvulus* (a filarial nematode) [6, 10, 12, 13, 15]. This parasite has previously also been associated with the *Nakalanga* syndrome (a tropical syndrome characterised by short stature and malnutrition) [16–18]. *O.volvulus* has in addition been associated with generalised epilepsy [19]. However, *O.volvulus* is endemic in many parts of Africa, Latin America and Asia where it causes corneal keratitis (river blindness) but nodding syndrome has only been reported in parts of Africa. *O. volvulus* has also not been observed in brain tissue. If *O. volvulus* is involved in the aetiology of nodding syndrome, alternative mechanisms other than direct parenchymal injury are likely.

We hypothesise that, nodding syndrome is a neuro-inflammatory disorder, caused by antibodies to antigens from either *O.volvulus* or its symbiont, *Wolbachia*, cross reacting with host neuron proteins (HNPs). Antibodies against HNPs such as the voltage-gated potassium channel complex (VGKC-complex) including the leucine-rich glioma inactivated − 1(LGI1) protein and contactin-associated protein-like-2 (CASPR2), the N-methyl-D-aspartate (NMDA), α-amino-3-hydroxy-5-methyl-4-isoxazolepropionic acid (AMPA), gamma amino-butyric acid (GABA)_A,_ GABA_B_ and glycine receptors are recognised in severe epileptic disorders [20]. Preceding infections may play a role, possibly through molecular mimicry or indirectly by inducing cytokines and allowing pathogenic antibodies gain access to the brain (reviewed in [20, 21]). Two pilot studies have specifically demonstrated evidence of possible cross-reacting antibodies in the pathology of nodding syndrome, including to leiomodin and DJ-1 [2, 22].

*O.volvulus* is transmitted by female blackflies of the genus *Simulium.* Infective larvae are injected into the host during a blood meal. These grow reaching maturity 1–3 years later. The adult worms reside in skin nodules where they can live for 10–15 years producing millions of microfilariae. These migrate under the skin and may be ingested by the next fly to continue the cycle [3]. Ivermectin kills the microfilaria but the adult worm has no specific drug treatment. However, antibiotic depletion of *Wolbachia,* the *O.voluvulus* symbiotic bacteria, with tetracyclines such as doxycycline, results in sterilisation and premature death of the adult worm and marked reduction in dermal microfilaria [23]. The outcome of nodding syndrome could potentially be improved with such a therapy that kills adult *O.volvulus*.

This study aims to examine the effects of treating patients with nodding syndrome, aged 8 years or older, with oral doses of doxycycline 100 mg daily for six weeks compared to placebo, on serum levels of antibodies to HNPs (VGKC complex, leiomodin, DJ-1 and others to be identified in a concurrent case-control study) at 24 months and on seizure control, disease severity, quality of life, ongoing inflammation and microfilaria density. It will also assess safety, adherence to treatment and factors associated with non-adherence.

## Methods

### Study design

This will be a two-arm double-blind parallel group, placebo-controlled phase II randomised trial of oral doxycycline 100 mg daily for six weeks, versus placebo, for the treatment of nodding syndrome.

### Setting

The study will be conducted in the nodding syndrome affected districts of northern Uganda and will be based in Kitgum General Hospital. The setup of this trial has been described elsewhere [24].

### Participants

Participants will be children and adolescents with confirmed nodding syndrome as defined by the WHO [25] i.e. A child who has experienced head nodding on two or more occasions, observed by a trained health worker or documented on EEG, with symptom onset between the ages of three and 18 years, plus any one of 1) triggered by food or cold weather; 2) presence of other seizures or neurological abnormalities and cognitive decline; 3) clustering in space or time in the local population.

### Sample size

From our pilot studies, ~ 50% of patients with prevalent nodding syndrome had antibodies to a HNPs and ~ 60% to leiomodin [2, 22]. We hypothesise that among patients with new onset nodding syndrome (symptoms < 12 months), six weeks’ therapy with doxycycline will cause a 50% reduction in the proportion of patients with and the levels or titres of antibodies to HNPs (a reduction from 50 to 25% compared to placebo) at 24 months. In Uganda, however, there has been no incident cases of nodding syndrome since 2014. It is anticipated that the intervention may not be as efficacious in patients with established symptoms (i.e. patients with symptoms ≥12 months) and the effect on antibodies would be smaller (an anticipated 40% reduction from 50 to 30%). To demonstrate this effect at 80% power and 5% level of significance and allowing for 10% losses to follow up, we will need to recruit a total of 230 patients with established symptoms (115 in either arm).

### Study procedures

Potential participants will be evaluated through a pre-randomisation phase involving outpatient screening, obtaining consent and enrolment. Consented participants will undergo an inpatient assessment phase, a randomisation and treatment initiation phase, an intervention phase and finally, a follow up and outcome determination phase, Fig. 1.

**Fig. 1 Fig1:**
[figure not shown]
Study design, flow and participant follow up and assessments. Figure is a schematic diagram that shows a time schedule of enrolment, interventions, assessments, and visits for participants

### Pre-randomisation phase

Potential participants will be identified in specialised nodding syndrome outpatient clinics or community outreach centres. Screening, assent and informed consent procedures will be performed in the same clinics and the community outreach centres by study staff. The inclusion criteria will be patients with confirmed nodding syndrome as defined by the WHO [25] and aged 8 years or older. Females with a positive urinary HCG (pregnancy) test (tested if the participant has experienced menarche), those anticipated to migrate away from the study catchment area, those with known hypersensitivity to tetracyclines, and those with suspected high likelihood of non-compliance to the study drug or follow-up schedule will be excluded. Patients on phenobarbitone, carbamazepine, or phenytoin will first be weaned off and put on sodium valproate, the standard of care antiepileptic drug, before enrolment.

### Inpatient assessment

After eligibility is confirmed and consent obtained, the subject will be hospitalised for 1–2 weeks in Kitgum General Hospital for baseline assessments. The patients’ treatment will be updated per standard of care protocols. The clinical assessment will include a review of the pregnancy, birth and developmental history, the past medical history, a description of the progressive development of the symptoms of nodding syndrome, and the burden and types of seizures. A detailed physical assessment will also be performed including a neurologic, psychiatric and cognitive examination. The Gross Motor Function Classification System (GMFCS) and the Modified Rankin Scale will be used to describe gross motor abilities. The Mini-International Neuropsychiatric Interview for Children and Adolescents (MINI-KID) [26] will be used to document psychiatric disorders and the disorders classified per the Diagnostic Statistical Manual (DSM)-V criteria; Intellectual Disability will be assessed using the Child and Adolescent Intellectual Disability Screening Questionnaire (CAIDS-Q) [27]; nutritional status will be assessed against WHO 2000 anthropometric standards; cognitive function will be assessed using the Cogstate - a computerised cognitive testing program [28], and the quality of life (QOL) will be assessed using the Quality of Life in Childhood Epilepsy (QOLCE) questionnaire [29].

All participants not on standard of care treatments will be initiated on therapy including sodium valproate for seizures, nutritional, physical and psychological therapy as appropriate. Patients receiving current standard of care treatment but with ongoing seizures will have their doses of sodium valproate optimised to 20-35 mg/kg/day.

Five-10mls of blood will be drawn for standard of care testing (full blood count, liver and renal function tests, and HIV). We will also obtain skin snips for *O.volvulus* microfilaria density (on microscopy and Real Time [RT] PCR) and *Wolbachia* load testing. Lumbar puncture will be performed and 3-4mls of cerebrospinal fluid obtained. Aliquots of plasma, serum and cerebrospinal fluid will be stored for baseline evaluation of study specific tests.

All will have a 30-min diagnostic electroencephalographic (EEG) recording. In addition, an overnight EEG will be obtained in a convenient sample of 45 participants selected by stratified random sampling to reflect the five clinical stages of nodding syndrome [30].

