#### Secondary efficacy outcomes

Key secondary efficacy measures at 24 months will include:Mean change in serum levels or titres of antibodies to HNPs or leiomodin and serum levels or titres of inflammatory markers.Mean change in dermal microfilaria density on real time PCR at 24 months.The proportions of patients achieving seizure freedom (≥1 month without head nodding or convulsive seizures), mean change in Cogstate scores, the proportions of patients with inter ictal epileptiform discharges on diagnostic EEG, proportion of participants with Gross Motor Function Classification System (GMFCS) scores 3–5; and the proportion of participants with mental health disorders on the MINI-KID and intellectual disability on the CAIDS-Q and the proportion of participants with improved Quality of Life.Others will be mean changes in weight-for-age, height-for-age (stunting), and height-for-weight (wasting) Z-scores and proportions of participants with wasting and stunting (Z-scores <− 3 SD)Incidence rate of non-nodding syndrome sick clinic visits and all cause sick clinic visits; incidence rate of all-cause hospital admissions and all-cause mortality

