### Statistical analysis

Analysis will be by intention to treat. The analysis will compare the proportions of patients testing positive for and the levels or titres of antibodies to HNPs or leiomodin at baseline and at 24 months in both arms. Both crude (unadjusted) and adjusted effect estimates will be computed. The chi square test will be used to compare proportions of children with the different antibodies in the two arms; the Students t-test will be used for means of normally distributed data and the Mann-Whitney U test for skewed data. We will also determine the mean change or reduction in the levels or titres of the antibodies and inflammatory markers with the intervention. Time to event (e.g. to seizure resolution) will be measured from the date of randomisation using Kaplan Meyer Survival analysis and by Cox regression analysis. For the cognitive tests, in addition to classification as impaired or not (in comparison to norms determined from unaffected sibling controls in the concurrent case control study), we will also measure mean improvements in scores. The rates determined will be adjusted for age, HIV infection, weight for height z scores and corrected for multiple testing. We will examine safety (serious adverse events and adverse events) and assess compliance and the factors for poor compliance.

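### The covariates named for the adjusted analyses omit baseline seizure burden and the pre-randomisation antiepileptic change, which can cost precision in the secondary seizure outcomes

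*Protocol article*

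**What the plan says.** Antiepileptic treatment can change in three ways before randomisation.

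- **Switched.** Under Pre-randomisation phase, patients on phenobarbitone, carbamazepine or phenytoin "will first be weaned off and put on sodium valproate, the standard of care antiepileptic drug, before enrolment". No interval between switch and randomisation is given.
- **Started.** Under Inpatient assessment, participants not yet on standard care begin it, including valproate for seizures, during a stay of 1 to 2 weeks.
- **Raised.** In the same section, patients already on standard care but "with ongoing seizures will have their doses of sodium valproate optimised to 20-35 mg/kg/day".

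The remaining patients are unchanged. Inpatient assessment also lists the burden and types of seizures among the baseline clinical facts collected.

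The Secondary efficacy outcomes section includes, at 24 months, "The proportions of patients achieving seizure freedom (≥1 month without head nodding or convulsive seizures". The Statistical analysis section adds: "Time to event (e.g. to seizure resolution) will be measured from the date of randomisation using Kaplan Meyer Survival analysis", and also by Cox regression. It says that both unadjusted and adjusted effects will be estimated, then names the adjustment set: "The rates determined will be adjusted for age, HIV infection, weight for height z scores and corrected for multiple testing". Randomisation is stratified by skin snip result only.

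**The concern.** Age, HIV infection and weight-for-height may be sensible covariates for other outcomes. For seizure outcomes one would first expect seizure burden at entry and what was just done to the antiepileptic treatment. The protocol makes those treatment changes in order to control seizures, and the time-to-event clock starts at randomisation, after them. Neither fact is in the named set or in the stratification.

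Leaving out a prognostic baseline factor lowers the power of the comparison and pulls an unadjusted Cox hazard ratio towards 1. It also lets a chance imbalance in that factor move the observed arm difference. Seizure control was not used to size the trial, yet it is the outcome singled out under Interim analyses for the added look when 132 participants reach 12 months. Precision there has not been planned for, so it is worth keeping what is available.

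**Working it through.** **1. The plan's own figure.** The sample size is built on antibodies: "the effect on antibodies would be smaller (an anticipated 40% reduction from 50 to 30" per cent, with "To demonstrate this effect at 80% power and 5% level of significance and allowing for 10% losses to follow up", to "recruit a total of 230 patients with established symptoms (115 in either arm").

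- Uncorrected n per arm = [1.96·√(2·0.4·0.6) + 0.8416·√(0.5·0.5 + 0.3·0.7)]² / 0.2² = (1.358 + 0.571)² / 0.04 = 93.
- With continuity correction: (93/4)·[1 + √(1 + 4/(93·0.2))]² = 102.8, so 103 per arm.
- Allowing for 10% loss: 103/0.9 = 114.4, so 115 per arm and 230 in total.

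The stated figure reproduces. It does not depend on seizure outcomes, so nothing below changes it.

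**2. Inputs for the seizure check.** Evaluable participants: 230 × 0.9 = 207, split 103 and 104. Test: two-sided 5%. The documents give no seizure-freedom rates, no share of patients with an antiepileptic change, and no expected doxycycline effect on seizures. These are assumptions: one yes/no baseline factor held by half the participants, a doxycycline odds ratio of 2.3 for 24-month seizure freedom, and a hazard ratio of 1.75 for time to resolution (exponential times, censored at 24 months). The factor stands for any baseline fact of the stated strength, whether treatment change or a split of baseline seizure burden.

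**3. Power by simulation.** For the proportion, the unadjusted chi-square test is compared with the Cochran-Mantel-Haenszel test stratified by the factor. For time to resolution, the log-rank test is compared with its stratified form.

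| Control-arm seizure freedom without / with the factor | 24-month proportion: crude → stratified | Time to resolution: crude → stratified |
|---|---|---|
| 15% / 60% (strong) | 63% → 73% | 61% → 76% |
| 15% / 45% | 71% → 77% | 60% → 68% |
| 30% / 50% (weak) | 82% → 83% | 77% → 79% |

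**4. Sensitivity at odds ratio 2.0** (103 per arm, half with the factor):

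- No predictor (30% / 30%): 68% → 67%, a difference of under one point before rounding.
- 30% / 50%: 64% → 67%.
- 20% / 60%: 53% → 61%.
- 15% / 70%: 38% → 52%.

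With odds ratios of 2.0 to 2.33 and the share varied from 25% to 75%, the most extreme contrast (15% / 70%) gains 10 to 17 points. I do not rest the point on that case, because it needs a 55-point contrast in seizure freedom to persist for two years.

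**5. Direction.** If the changed group does worse instead of better, the two strata merely swap labels. At a 50% share the gain is identical by construction. At a 25% share, reversing 20% / 60% is the same as the unreversed case at a 75% share. The gains there are 54% → 60% (25% share) and 57% → 62% (75% share), about 5 points either way.

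**6. Type I error.** With no treatment effect, rejection is about 5% with or without stratification.

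**7. Chance imbalance.** The standard deviation of the between-arm difference in the share with the factor is √[0.25·(1/103 + 1/104)] = 0.0695. Then 1.96 × 0.0695 = 0.136. Multiplied by a 0.30 to 0.45 difference in seizure freedom, this gives 4.1 to 6.1 percentage points of possible movement in the crude arm difference (95% range). This is the same imprecision seen from another side, not a further loss.

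**The case against.** Several points on the other side carry weight.

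- **The plan already promises adjustment, and Cox regression takes covariates.** This stands: it would be wrong to say that the seizure analyses are only crude. What remains is the choice of covariates and the lack of a designated main estimate. If the covariate sentence was not meant to cover seizure outcomes, then no covariates are named for them at all, and the request is the same.
- **Covariates for secondary models usually belong in the analysis plan, which is not shown.** A longer list there would settle the matter. But the article does not stay silent: it names a set, and an analysis plan that follows it would inherit the gap.
- **The documents do not establish that valproate will make the changed group do better.** A reader might infer that seizure freedom driven by valproate in both arms will hide a doxycycline effect. The text does not support that. Doses are raised because seizures continue, so the changed group may be the harder one to control. Indication and drug benefit may also offset each other and leave a weak predictor. The gain depends on the strength of the association, not its sign, but this is why baseline seizure burden belongs beside treatment change.
- **Adjustment cannot remove a ceiling.** If doxycycline converts 20% of those not already seizure free, power with 103 per arm falls from 73% at a 20% control rate to 16% at 70%. No covariate recovers that.
- **Persistence and recording are uncertain.** A change made before randomisation need not still predict seizure freedom at 24 months. The Concomitant drugs section covers medication taken during the study, so it may not capture a switch made before enrolment.

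**Conclusion.** The point holds as a matter of precision in secondary outcomes. The named covariates omit baseline seizure burden and the antiepileptic change, both of which plausibly predict seizure outcomes. Under the assumptions shown, adjusting for such a factor gains about 0 to 1 power points for 24-month seizure freedom when it predicts weakly or not at all, and about 10 when it predicts strongly. Under the same assumptions the gain for time to resolution runs from about 2 to 15 points. All of these sizes depend on assumed rates, so the documents do not show that the loss is material, only that it could be.

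A reader might go further and infer bias, or a threat to the trial's main conclusion. Neither follows. The change precedes blinded randomisation and is balanced in expectation, type I error stays at about 5%, and the primary antibody outcome and the 230 are unaffected. It is a modest improvement at very low cost.

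**What to change.** In the Statistical analysis section, or in the analysis plan before allocations are disclosed, name the main estimate for the two seizure outcomes:

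- for seizure freedom at 24 months, a logistic model, and for time to seizure resolution, a Cox model;
- each adjusted for baseline seizure burden and for antiepileptic change before randomisation (none, raised, started, switched), as far as this is recorded;
- with the crude estimate reported alongside.

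Valproate dose in mg/kg/day at randomisation may be added but is optional, because it overlaps with both covariates. Confirm that the baseline forms capture switches made before enrolment; if they do not, reduce the categories to what was recorded.

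The cost is a sentence or two of analysis wording and a few degrees of freedom. The odds or hazard ratio becomes conditional on the covariates, which should be stated when it is reported. No change to treatment is proposed.
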